#### *Secondary endpoints*

Health Related Quality of Life (GIQLI and EQ-5D-3L): HRQoL will be evaluated by the Gastrointestinal Quality of Life Index (GIQLI) and EuroQol five dimensions questionnaires (EQ-5D-3L, EuroQol group) which assess the physical and mental health of IBS patient.

The GIQLI questionnaire  is a specific self-questionnaire for measuring the quality of life of patients with gastrointestinal disease. The questionnaire includes 36 items asking about symptoms, physical status, emotions, social dysfunction, and effects of medical treatment.

The quality of life questionnaire "EQ-5D"  is a non-specific questionnaire used to assess the health status and the impact of a disease on patient's quality of life. The EQ-5D score is measured on 5 dimensions (mobility, personal autonomy, routine activities, pain and anxiety/depression) with three levels per dimension and a scale from 0 (worst imaginable state of health) to 100 (best imaginable state of health).

These assessments are done at every planned visit.

IBS severity (IBS-SSS and Bristol scale): IBS-SSS questionnaire  is a self-administered questionnaire used to assess the severity of the specific symptoms related to IBS. This questionnaire consists of 7 questions giving a score between 0 and 500 points. IBS intensity is considered mild for a Francis score less than 175, moderate for a score from 175 to 300 and severe if the score is above 300.

The scale of Bristol is a medical diagnostic tool created to classify the shape and consistency of human faeces. The scale has seven distinct categories. This assessment is done at home by the patient alone, every week before planned visits, on the daily logbook (the evening (before bed): stools number and consistency).

#### Genetic analysis of cytochromes P450:

A blood sampling (1 tube of 6 ml) will be performed for the genetic analysis of the genes coding for CYP3A4 and CYP2E1, involved in the metabolism of ethosuximide. This genetic analysis will make it possible to demonstrate the existence (or not) of slow / fast metabolizers in our studied population. The demonstration of slow / rapid metabolizers will enable us to carry out a more precise analysis on the therapeutic efficacy of ethosuximide.

These blood samples will be strictly used in this study and a specific document informing the patient and obtaining his authorization will be provided during the first visit (D0-7).

Analgesic and antispasmodic/regulators transit consumption: Drugs consumption for IBS will be evaluated throughout the study

Safety: Any adverse events were collected daily by the patient and during the planned phone calls by investigators (every 7 days). Adverse events are categorized according to their type, intensity and treatment related by investigators. Due to the long half-life of ethosuximide (60h), a phone call, within 3 weeks after stopping treatment, will be allowed to recover any adverse effects.

Study discontinuation rate will be evaluated and compared in the two treatment arms.

#### Participant timeline (see figure 1):

The duration of treatment is 12 weeks. The total duration of patient participation is maximum 16 weeks. The protocol includes 5 visits (Day0-7, Day0, Day0+4 weeks, Day0+8 weeks and Day0+12 weeks).

#### Sample size:

According to previous work presented in literature, we have estimated that a sample size of  $n = 130$  patients per randomized group, for a two-sided type I error at 5%, would provide 90% statistical power of detecting an absolute difference of 20% between ethosuximide and placebo in the primary outcome: rate of responders to treatment as defined previously (35% for placebo and 55% for ethosuximide). Finally, a total of  $n=290$  patients (145 by group) will be considered to take into account lost to follow-up (10%). An interim analysis will be performed after 100 included patients to analyse safety and effectiveness in order to recalculate the sample size according results.

#### Enrolment:

At least ten clinical sites participate in France, all specialized in the treatment of IBS. The recruitment will be spread over 30 months with 1 patients/month/centre, which seems to be largely sufficient in the recruitment potential (prevalence of IBS = 15% in French population []).

#### Assignment of interventions:

Allocation Sequence generation: computer-generated random numbers. Stratification by centre and 6 blocks random sequence.

Allocation concealment: sequentially numbered.

Implementation: Biostatistician generates the allocation sequence, investigators enrol participants and Clinical Research Associate (CRA) assigns participants to interventions.

#### Blinding:

All participants to study are blinded (double-blind trial). Unblinding is possible only in case of serious adverse event or at the end of study if the study treatment showed a convincing therapeutic effect (Possibility of prescribing the treatment out of the study).

#### Data collection, management, and analysis:

##### *Data collection methods*

Data entry will be made by the investigators and CRA of each clinical centre, at each planned visits and during the ambulatory period.

Data entry will be centralized in the coordinating centre (CHU Clermont-Ferrand), from an electronic case report form (e-CRF, Ennov Clinical, France) filled-in during site visits.

All patients will be analysed (intent to treat analysis). However, if a major deviation from the protocol (non-respect of co-occurring treatment, inclusion / exclusion criteria and the study design) only safety data will be evaluated.

##### *Data management*

A consistency test will be conducted to validate compliance of data entered in accordance with the study protocol.

##### *Statistical methods*

Statistical analyses will be conducted using Stata software (version 13, StataCorp, College Station, US). A two-sided p-value of less than 0.05 will be considered to indicate statistical significance (except interim analysis).

Intent-to-treat (ITT), mITT, and per-protocol (PP) analyses were performed for the primary endpoint and expressed as relative risks (RR) with 95% confidence intervals (CI). Non-compliant patients were considered non-responders. Responder rates were compared using the chi-squared test and a pre-specified multivariate analysis was performed using a generalized linear mixed model (Poisson regression with a log link and robust variance 26) accounted for fixed covariates (e.g., gender, IBS subtype) and centre-level variability were performed. Primary endpoint components were also analysed with the Hochberg procedure for multiple testing.

Continuous outcomes were assessed with linear mixed models incorporating patient-level random effects (slope and intercept) nested within centre-level random effects. Results were expressed as regression coefficients (standardized mean differences - MD) with 95% CI, based on the interaction between time and randomization group. The normality of residuals from these models was analysed as aforementioned. Safety analysis was conducted with chi-squared or Fisher's exact tests.

Missing data (if any) were imputed using Multiple Imputation by Chained Equations (MICE). Analyses were conducted using Stata 15.0, with a two-sided P value <0.05 considered significant, and the widths of confidence intervals were not adjusted for multiplicity and should not be used as a substitute for hypothesis testing, except for the primary outcome and its composite components. An interim analysis is planned after enrolment of the first 100 patients using the Lan and DeMets rule (East software, Cytel Inc, Cambridge, Massachusetts, US). The type I error is fixed at 0.03 for this interim analysis. In addition, an early intermediate analysis (third of the inclusions) will be also proposed in order to study safety of the initial maximum dose (10 ml/day) and, if necessary, to allow the addition of a therapeutic dose in case of inefficiency.

According to clinical relevance and to EMA and CONSORT recommendations, sub-group analyses depending on IBS subgroup and gender will be proposed after the study of sub-group x randomization group interaction in regression models (for repeated data or not). A descriptive analysis of stopping and discontinuations in view of dose escalation will be considered. A particular focus will be done to safety and loss to follow-up. A study of abandonment considered as censored data will be proposed using the Kaplan-Meier estimation.

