#### 1.7 Sample size

According to previous work presented in literature, we have estimated that a sample size of  $n=130$  patients per randomised group, for a two-sided type I error at 5%, would provide 90% statistical power of detecting an absolute difference of 20% between ethosuximide and placebo in the primary outcome. Based on the meta-analysis of Ford et al, the estimated median responder rate in the placebo group was 35%. A slightly higher rate than the previously mentioned meta-analysis (32% of responders under drug therapies), in order to avoid underestimating the placebo effect. Finally, a total of  $n=290$  patients (145 by group) was considered to take into account lost to follow-up (10%). A blinded interim analysis was planned after enrolment of the first 100 patients using the Lan and DeMets rule (East software, Cytel, Cambridge, Massachusetts, USA) to study safety of study treatment (ethosuximide and placebo) and efficacy, to continue or stop the study in case of futility and to recalculate the number of patients needed. The type I error is fixed at 0.03 for this interim analysis.

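### The 90% power at a two-sided 5% error makes no allowance for the 0.03 interim look, and the rule for lost and non-compliant patients that the power depends on is not settled

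*Combined protocol and SAP*

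**What the plan says.** **Sample size (protocol, Sample size; SAP 1.7).** The design takes 130 per group, a two-sided 5% error and responder rates of "35% for placebo and 55% for ethosuximide". This "would provide 90% statistical power of detecting an absolute difference of 20% between ethosuximide and placebo". The total is then raised to 290 (145 per group) for 10% loss to follow-up. No other adjustment is described.

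**Interim (protocol, Statistical methods; SAP 1.7).** A Lan and DeMets analysis is planned after the first 100 patients: "The type I error is fixed at 0.03 for this interim analysis". The protocol says it covers safety and effectiveness and serves to recalculate the sample size. SAP 1.7 calls it blinded, lists safety and efficacy, and names a futility stop and recalculation as its outcomes. No spending function and no final boundary are given.

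**Final test.** The protocol (Statistical methods) sets 0.05 two-sided, with an exception for the interim only. SAP 2.4 sets 0.05 for all analyses.

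**Lost and non-compliant patients.** The rules differ from place to place:
- Protocol, Statistical methods: "Non-compliant patients were considered non-responders". The same section sends missing data to multiple imputation (MICE).
- Protocol, Data collection methods: everyone is analysed as randomised, but after a major deviation only safety data count.
- SAP 2.1 lists ITT, modified ITT and per-protocol populations for the primary analysis. SAP 2.2 says the ITT population will not be analysed, and removes patients with no primary outcome or with non-compliance from the other two.
- SAP 2.4 leaves the imputation method open among several.

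**The concern.** The sample size treats the final test as the only test. It spends the full 5% there and takes no account of a look that has been assigned 0.03. A type I error allotted to an interim has to come out of the total, or the total exceeds 5%. Either the error or the power is therefore not what the plan states, provided the interim can reject.

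The inflation from 130 to 145 also presumes that lost patients leave the analysis and that those who remain still show 35% against 55%. That fits exclusion, and roughly fits imputation under missing at random. It does not fit scoring lost patients as non-responders, which keeps them in the denominator and lowers both rates.

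The stake is how the result is read. After a negative trial, readers will take 90% as the chance it had of detecting 20 points. After a positive one, they will take 5% as the chance of a false positive.

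**Working it through.** **Inputs from the documents:** 35% and 55%; 130 and 145 per group; 10% loss; two-sided 0.05; 0.03 at 100 of 290 patients; 1:1 allocation (SAP 1.4). **Assumptions:** the interim can reject for efficacy at a two-sided 0.03; the information fraction is 100/290 = 0.345; N stays at 290.

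**1. Reproduce the plan's figure.** Pooled-variance power for two proportions, with p̄ the mean of the two rates:

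Power = Φ{ [ |p2 − p1|·√n − z·√(2p̄(1 − p̄)) ] / √(p1(1 − p1) + p2(1 − p2)) }

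With n = 130 and p̄ = 0.45: (0.20 × 11.402 − 1.960 × 0.7036) / 0.6892 = 1.308, so power is 90.5% (128 per group would reach 90%). For the loss, 130/0.9 = 144.4, rounded up to 145. Both stated figures are right for one look at 5%.

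**2. Overall error as written.** The interim and final statistics have correlation √0.345 = 0.587. The interim cut-off at 0.03 is |z| = 2.170. With a final cut-off of 1.960, the probability under the null of crossing at either look (bivariate normal) is 0.0715, about **7.2%**.

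**3. Final level that holds 5%.** Solving for a final cut-off that gives a total of 0.05: z = 2.234, a nominal two-sided level of **0.0255**.

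**4. Power with that boundary.** Simulated with 1,000,000 runs; interim 2.170, final 2.234. The normal approximation is in the last column.

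| Handling of the 10% lost | n per group | Rates | One look at 0.05 | 0.03 spent, 5% total | Normal approx. |
|---|---|---|---|---|---|
| Excluded (or imputed under MAR, roughly) | 130 | 35% v 55% | 90.5% | **86.7%** | 86.0% |
| Scored as non-responders | 145 | 31.5% v 49.5% | 88.1% | **83.8%** | 83.2% |
| No loss at all | 145 | 35% v 55% | 93.2% | 90.3% | 89.7% |

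The first row has 45 evaluable per group at the interim (100 × 0.9 / 2). With 50 it is 87.0%.

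Diluted rates: 0.9 × 35% = 31.5% and 0.9 × 55% = 49.5%, a difference of 18 points. With p̄ = 0.405: (0.18 × 12.042 − 1.960 × 0.6942) / 0.6825 = 1.182, which gives 88.1%.

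**5. Power if the final test stays at 0.05 after the look.** 91.4% with 130 evaluable per group, and 88.7% with non-responder scoring at 145. On that reading the cost is the 7.2% error and not lost power.

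**The case against.** **The interim may not be able to reject.** SAP 1.7 calls it blinded and names only a futility stop and a recalculation. If efficacy cannot be declared there, no error is spent, and 90.5% power at 5% stands for 130 evaluable per group. This is the strongest answer, and it makes the point conditional. It does not remove it: both documents include efficacy in the interim and attach a Lan and DeMets rule and a type I error of 0.03, which have a purpose only if a rejection is possible.

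**The final test is stated at 0.05, so the interim does not lower power.** Correct as written. The excess then falls on the type I error, while the sample size section still claims 5%.

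**The planned recalculation could restore power.** It could, so any figure at 145 per group is provisional. But neither document gives a target power, a rule or a cap, so the recalculation does not make the stated figure true.

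**Dilution alone is small.** It takes 90% to 88.1%, under 2 points, which is well within the uncertainty of the assumed response rates. By itself it would not justify a comment.

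**Conclusion.** The point holds in conditional form. With the plan's own 10% loss and a 0.03 look that can reject at 100/290 of the information, either the overall type I error is about 7.2% (final test at 0.05), or power is about 87% (5% held, 130 evaluable per group). It does not depend on how lost patients are scored; non-responder scoring would take the second figure to about 84%.

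Two stronger readings are tempting, and the documents do not support them.

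- *The plan scores the 10% lost as non-responders, so the 20-point effect shrinks to 18.* No section says this. The non-responder sentence covers non-compliant patients, and the protocol ties compliance to counting treatment units at visits. Missing data go to MICE in the same section, and SAP 2.2 excludes patients with no outcome. The defect is that the rules conflict, so 88% and 84% are figures for one possible choice.
- *90% power and 5% error can never both hold.* With all 145 per group evaluable at 35% v 55%, power is about 90% even with the 0.03 spend. The shortfall appears once the planned 10% loss occurs.

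Nor do the documents give a basis for assuming different dropout in the two arms, so no figure is offered for that.

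**What to change.** 1. State in the protocol (Statistical methods) and SAP 1.7 whether the interim can stop for efficacy. If it can, set the final boundary so that the total is 5%: a nominal level of about 0.0255 if 0.03 is spent at 100/290, recomputed for the actual information fraction. If it cannot, remove the 0.03 efficacy spend and keep 0.05 at the end. Align the general 0.05 statements in the protocol and SAP 2.4 with the choice.
2. Name one rule for lost patients and one for non-compliant patients in the primary analysis, and make the protocol (Statistical methods and Data collection methods) and SAP 2.1, 2.2 and 2.4 agree with it.
3. Restate the power in the protocol's sample size section and SAP 1.7 for that combination. If 0.03 is spent within 5%, it is about 87% with exclusion or imputation under missing at random, and about 84% with non-responder scoring of the lost. Give the dropout assumption, and say that the figure is provisional on the sample-size recalculation.

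The cost is wording and one decision about the boundary, to be made before unblinding. No extra patients are needed for this correction. The downside is a less favourable stated power or, if the interim can reject, a stricter final threshold.

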Planned subgroup analyses were assess heterogeneity of the effect of ethosuximide on the primary outcome measure in pre-specified subgroups of patients with IBS subgroup and gender. According to usual recommendations, the interactions between group randomization and subgroups was evaluated in regression models (i.e., random-effects models, linear or generalized linear).

A descriptive analysis of stopping and discontinuations in view of dose escalation was considered. A particular focus was done to safety and lose to follow-up. A study of abandonment considered as censored data was proposed using the Kaplan-Meier estimation. The proportional-hazard hypothesis was verified using Schoenfeld's test and plotting residuals.

Finally, a sensitivity analysis was performed and the nature of missing data was studied (missing at random or not). According to this, the most appropriate approach to the imputation of missing data was proposed (MICE, spline interpolation, LOCF, BOCF...).

A two-sided P value of less than 0.05 was considered for statistical significance of all analyzes. The Hochberg procedure was used to adjust for multiple testing of each component of the composite primary outcome ((1) decrease of at least 30% of the intensity of abdominal pain (11-point NRS) compared with the score before treatment and (2) significant global improvement defined by a score of 4 or 5 on the SGA scale). Because of the potential for type 1 error due to multiple comparisons, findings from analyses of secondary endpoints were interpreted as exploratory.

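### The 0.03 fixed for the interim, the 0.05 kept for the final test and the single-test 90% power do not fit together, and neither document says whether the interim can declare efficacy

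*Combined protocol and SAP*

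**What the plan says.** **Interim level.** Protocol, Statistical methods, and SAP 1.7 both plan an interim analysis after the first 100 patients under the Lan-DeMets rule, and both add: "The type I error is fixed at 0.03 for this interim analysis".

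**Final level.** Protocol, Statistical methods, opens with "A two-sided p-value of less than 0.05 will be considered to indicate statistical significance (except interim analysis"), so only the interim is exempt. SAP 2.4 is broader: "A two-sided P value of less than 0.05 was considered for statistical significance of all analyzes".

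**Sample size.** Protocol, Sample size, sets 130 per group "for a two-sided type I error at 5%, would provide 90% statistical power", for responder rates of "35% for placebo and 55% for ethosuximide". It then raises this to 145 per group for 10% loss to follow-up. SAP 1.7 repeats the figures. Neither includes an allowance for the interim.

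**Purpose of the interim.** Protocol, Sample size, says it examines safety and effectiveness so that the sample size can be recalculated. SAP 1.7 calls it blinded, lists safety and efficacy, and names futility as the ground for stopping, together with recalculation of the number of patients.

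No spending function, final boundary or efficacy stopping rule appears in either document.

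**The concern.** A Lan-DeMets design divides one overall alpha among the looks. If 0.03 of a 5% budget is spent at the first look, the last look cannot also be tested at 0.05. The 130 per group assumes that it can.

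This is the threshold for the only primary endpoint. If 0.03 has been spent on efficacy, a final p-value between about 0.026 and 0.05 would be significant under the printed rule and not significant under a 5% Lan-DeMets design. The trial's conclusion would then depend on which sentence is followed, and that choice could be made after the data are seen.

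**Working it through.** **Inputs.** Rates of 35% and 55%, two-sided 0.05, 130 per group, 145 after 10% loss (Protocol, Sample size). 1:1 allocation (SAP 1.4). Interim at 100 patients, level 0.03, taken as two-sided (Protocol, Statistical methods; SAP 1.7). The information fraction t is not stated. I assume information proportional to patients and use 100/290 = 0.345 and 100/260 = 0.385.

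**1. The plan's own figure.** The mean rate is 0.45, so the null term is √(2 × 0.45 × 0.55) = 0.7036 and the alternative term is √(0.35 × 0.65 + 0.55 × 0.45) = 0.6892.
- n = (1.960 × 0.7036 + 1.2816 × 0.6892)² / 0.20² = 127.9, so 128 per group.
- Power at 130 = Φ[(0.20 × √130 − 1.960 × 0.7036) / 0.6892] = Φ(1.308) = 90.5%.
- 130 / 0.90 = 144.4, so 145 per group.

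The stated size reproduces, as a design with one test at the full 0.05.

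**2. Overall error with 0.03 then 0.05, if the interim can reject.** The two statistics are bivariate normal with correlation √t. The critical values are 2.170 and 1.960, and the error is 1 − P(|Z1| < 2.170, |Z2| < 1.960).

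| t | overall two-sided error |
|---|---|
| 100/290 | 7.15% |
| 100/260 | 7.06% |

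If 10% of the 100 lack an outcome, t = 90/260 and the error is again 7.15%. With 72 of the 100 evaluable (an illustrative assumption) it is 7.30%.

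**3. Final level if 5% is held and 0.03 is spent.** Solve 1 − P(|Z1| < 2.170, |Z2| < c) = 0.05 for c.

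| t | c | final two-sided level |
|---|---|---|
| 100/290 | 2.234 | 0.0255 |
| 100/260 | 2.223 | 0.0262 |

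**4. Power with those boundaries.** The final statistic has mean 1.960 + 1.308 = 3.268 at 130 per group, and the interim mean is 3.268 × √t.
- Overall power, rejecting at either look: 86.2% (100/290) and 86.5% (100/260). Using the variance under the alternative gives 86.1% and 86.4%.
- Final test alone: 84.8% and 85.1%.
- If all 145 per group were evaluable, overall power would be about 90% (89.7% to 90.1% across the same choices).

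**5. Comparison with common spending functions, total 0.05.**

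| function | spent at t = 0.345 | spent at t = 0.385 |
|---|---|---|
| O'Brien-Fleming type, 2[1 − Φ(1.960/√t)] | 0.0008 | 0.0016 |
| Pocock type, 0.05 × ln[1 + (e − 1)t] | 0.0233 | 0.0254 |

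The 0.03 matches neither. After O'Brien-Fleming-type spending the final level is 0.0496 or 0.0493, and power at 130 per group is 90.4%.

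**6. Chance of an early efficacy rejection under 35% versus 55%.** At 0.03 it is Φ(3.268 × √t − 2.170): Φ(−0.251) = 40% and Φ(−0.143) = 44%. With the O'Brien-Fleming-type boundary (3.338 or 3.160) it is 8% and 13%.

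**The case against.** The strongest reply is that no efficacy stop is planned. SAP 1.7 calls the interim blinded and names a stop only for futility, and the protocol's sample size section ties it to recalculation. A futility stop cannot raise the type I error. This stands as a condition on the 7%. A reader might infer that the trial's error rate simply is about 7%. The documents do not support that, because no sentence says that efficacy can be declared at 100 patients.

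The reply does not clear the text, though. Both documents list efficacy among the matters examined, invoke an alpha-spending rule and assign a type I error. An interim type I error has meaning only where the null hypothesis can be rejected. Nor does blinding settle the matter: SAP 1.5 counts the analysing statistician among those blinded, so the word may mean masked group labels, which still permit a comparison of arms.

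A second reply is that applying Lan-DeMets would itself yield a reduced final boundary. Total error would then stay at 5%. That is fair, and it means that the 7% and the 86% are alternatives, not joint consequences. But the printed 0.05 would then be wrong, and 130 per group would no longer give 90%.

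A third is that 145 per group are randomised and the sample size may be recalculated. Power returns to about 90% only if all 145 are evaluable, yet the extra 15 are there to cover the planned loss. Recalculation could restore power, but no rule for it is given.

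**Conclusion.** The contradiction holds under every reading, but which figure is wrong depends on a decision that the documents do not record.

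- **Interim can reject, final test at 0.05 as printed:** overall two-sided error of about 7.1% to 7.2%.
- **Interim can reject at 0.03, 5% held:** final level of about 0.0255 to 0.026 and overall power of about 86% at 130 evaluable per group. The printed 0.05 and 90% are then wrong.
- **Interim cannot reject for efficacy:** no inflation from this source, 0.05 stands, and the 0.03 is the error.

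The arithmetic is firm. The premise that an efficacy test is planned is not. The figures assume information proportional to patients and a fixed maximum sample size. They leave out any effect of an unblinded sample size recalculation, and of the additional early analysis at a third of inclusions (Protocol, Statistical methods), for which no alpha is stated.

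**What to change.** State in both documents whether the interim can reject the null hypothesis for efficacy, and what blinded means for that analysis.

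**If it can, choose one:**
- (a) Replace the fixed 0.03 with a named Lan-DeMets spending function at overall two-sided 0.05, and print the resulting final boundary. With an O'Brien-Fleming-type function, the interim level is about 0.001 to 0.002, the final level about 0.049 and power about 90.4%. Lan-DeMets does not require this particular function. It costs no patients, but the chance of stopping early for efficacy under the planned effect falls from about 40–44% to about 8–13%.
- (b) Keep 0.03, print a final level of about 0.025 and restate power as about 86% at 130 evaluable per group. The cost is the lost power, or a larger trial. By the formula in step 1 with 0.025 in place of 0.05, 90% for the final test alone needs 152 evaluable per group, or 169 randomised (152 / 0.90 = 168.9).

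**If it cannot:** delete the 0.03 and the Lan-DeMets efficacy wording, and keep the final test at 0.05. This changes wording only.

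In every case, amend the general significance sentences in the protocol's statistical methods and in SAP 2.4 to agree with the choice. Say whether the sample size recalculation uses pooled data or unblinded effect estimates. If it uses unblinded estimates, the boundaries above are not sufficient and the final test must also account for that. Say too whether the early analysis at a third of inclusions compares efficacy between arms.
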